**Figure 2 F2:**
[figure not shown]
Study design.

Both process and impact evaluations will be carried out using mixed methods. Primary and secondary nutrition outcomes include longitudinal difference-in-difference analyses of parameters – height-for-age *Z* score, stunting prevalence, child fish food intake, child dietary diversity, and child diarrheal morbidity. Other outcomes include awareness of the social marketing campaign and knowledge transfer. Primary and secondary fisheries outcomes will be longitudinal difference-in-difference analyses in fisheries yield of mature fish and fisher income and earnings.

The *Samaki Salama* intervention precludes randomization due to the high risk of spill-over effects and the limited number of trap fishers with children under the age of 5. Thus, for the impact assessment, we will conduct a matched intervention/control design to minimize selection bias and test effectiveness on nutrition and fisheries production. Steps have been taken to reduce the risk of selection bias that might arise from the matched design. A pilot study and additional formative research will be used to identify and match communities on important characteristics [socioeconomic status (SES), child nutrition, livelihoods, etc.]. This preliminary data provides additional information needed for external validity and extrapolation of findings to other small fisher households in Kenya and internationally. The longitudinal difference-in-difference design further contributes to the internal validity, accounting for residual confounding, and increases the statistical power to detect intervention effects.

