### Sample size

Sample size calculations for the cluster design applied a mean −1.3 height-for-age (HAZ) for the coast region (20) and a hypothesized 0.20 effect size (21). Thus, we estimate requiring a total sample size of 400 households, which includes ~4 clusters per arm (four villages per BMU) and 50–75 households per cluster – assuming 20% losses-to-follow-up (α = 0.05 and 1-β = 0.80). Although this is small number of clusters, we will apply matching techniques a priori and during data analyses (e.g., propensity score matching) to better ensure internal validity.

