### Participant eligibility, recruitment, and retention

At the outset of the study, we will identify comparable communities associated with BMUs on the coast of Kilifi County using potential confounding variables: proximity to shoreline or ability to participate in the fishery; presence of no-take fisheries closures; composition of fishing gears used; background nutritional status; usual diets; income and assets; and access to market information. We will draw on existing relationships and data from communities where formative research was previously conducted by the project team. BMU leaders and other stakeholders will be convened to first inform them of the potential project and solicit permission to act in partnership with BMUs to conduct the research.

To be eligible to participate in the study, an individual must meet all of the following criteria:
A household member works in small-scale fisheries (self-employed fishers).At least one child in the household aged 6–60 months.Provision of signed and dated informed consent form.For children, informed assent and parental informed consent to participate in the study.Stated willingness to comply with all study procedures and availability for the duration of the study.

An individual who meets any of the following criteria will be excluded from participation in the study:
No household member works in small-scale fisheries (self-employed fishers).No child in the household aged 6–60 months.Declines to sign the informed consent.Index child is severely malnourished.Lives outside the study area.Participation in another nutrition or fisheries intervention study within April 2021 - June 2022.

We anticipate a total sample size of 400 small-scale fisher household units (mother, father, and child 6–60 months). There will be 100 in each intervention group (social marketing and social marketing plus modified traps) and 200 in the control group. Table 2 provides a summary of the total number of individuals and anticipated demographics.

**Table 2 T2:** Sample size and demographics.

**Group 1: Control (n = 200)**			**Group 2: Social marketing (n = 100)**			**Group 3: Social marketing + modified traps (n = 100)**		
**Group**	**# of individuals**	**Anticipated sex**	**Group**	**# of individuals**	**Anticipated sex**	**Group**	**# of individuals**	**Anticipated sex**

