### Analysis

#### Primary and secondary outcomes

Generalized linear regression modeling (GLM), allowing for non-normal distributions, will test the continuous outcomes of HAZ, WAZ, child dietary fish intake, child dietary diversity score, fisheries yield, and fish earnings. As a difference-in-difference analyses, change variables for each outcome will be examined (difference between baseline and endline). For the binomial outcomes of diarrhea morbidity (and other outcomes of stunting and underweight), we will estimate prevalence ratios by the GLM modeling with robust Poisson. If stunting prevalence in this population exceeds the acceptable threshold for use of odds ratios (0.2105), prevalence ratios (PRs) will be used to examine the intervention effect and were considered analogous to relative risk in this longitudinal study. The robust Poisson, with a classic sandwich estimator to correct the inflated variance of standard Poisson, is less affected by outliers.

To test for intervention effectiveness, the two intervention groups will be combined for all hypotheses except the secondary outcome of increased fisher earnings and exploratory hypothesis for differences between social marketing and social marketing + traps intervention groups. Regression models will be adjusted for potential confounding factors including age, sex of the child, corresponding baseline measures, and others found to differ significantly between the trial groups (e.g., maternal education). For fisheries yield, confounding factors will be used to adjust regression models, such as: water temperature, fishing ground area, coral cover, and seasonality. The *P* significance value for Type I error (and one-tailed test) will be *P* < 0.05 and corresponding 95% confidence interval. Diagnostics for regression model assumptions, structure and observations will be applied, and corrective procedures applied as necessary. If selection bias is widely detected with important differences across intervention and control communities, we will apply propensity score analyses (36). Data analyses will be performed with Stata software (version 16.0; StataCorp, College Station, TX) and R (4.1.2).

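### Child-outcome covariates beyond age, sex and baseline value enter only if they differ significantly between non-randomised groups, so confounders named in advance can be left out

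*Protocol article*

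**What the plan says.** All references are to the protocol article.

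- **Design.** The "intervention precludes randomization due to the high risk of spill-over effects" and the limited number of eligible trap fishers. Communities are matched instead, and outcomes are analysed as difference-in-difference.
- **Analysis, primary and secondary outcomes.** "Regression models will be adjusted for potential confounding factors including age, sex of the child, corresponding baseline measures", and then "others found to differ significantly between the trial groups (e.g., maternal education").
- **The same paragraph, fisheries yield.** Covariates are named outright, "such as: water temperature, fishing ground area, coral cover, and seasonality", with no significance condition.
- **Participant eligibility, recruitment, and retention.** The potential confounders used to find comparable communities include "presence of no-take fisheries closures; composition of fishing gears used; background nutritional status; usual diets; income and assets; and access to market information".
- **Study measures, end of the secondary outcomes.** Child illness, household consumption and assets, and household decision making are to be measured in order to control confounding.
- **Sample size.** After conceding that clusters are few, it says "we will apply matching techniques a priori and during data analyses (e.g., propensity score matching) to better ensure internal validity".
- **Analysis.** "If selection bias is widely detected with important differences across intervention and control communities, we will apply propensity score analyses". It states no measure of balance.

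**The concern.** Without randomisation, confounding is the main threat to the child comparisons. A variable biases the estimate by its imbalance between groups multiplied by its effect on the outcome. A baseline significance test looks only at the first factor, and measures it against a standard error set by the number of households and clusters. With about four clusters per arm, a test that respects the design will rarely flag a moderate imbalance, however strongly the variable affects growth.

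The article has already identified plausible confounders on subject-matter grounds, in the matching list and again under Study measures. The child models do not commit to using them. As written, they must first pass the screen. The yield model in the same paragraph needs no such screen, so the better practice is already in the plan for one outcome.

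The propensity analysis is the stated safeguard for having few clusters, yet the Analysis section makes it depend on what the data show.

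**Working it through.** **Inputs from the article.** 400 households, 200 control and 200 intervention when the two intervention groups are combined; about 4 clusters per arm of 50-75 households; target 0.20 HAZ; 20% loss; power 0.80; alpha 0.05, one-tailed for outcomes.

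**Assumptions.** A confounder with a true imbalance of 0.20 SD; a two-sided 5% balance test; 4 v 4 clusters of 50 (4 × 50 = 200 per side); ICC 0.02, 0.05 or 0.10; an effect of 0.1-0.4 HAZ change per SD of the confounder. The article gives none of these.

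**The plan's own figure.** No SD or ICC is stated, so 400 can be neither confirmed nor refuted. Ignoring clustering, two-sided, n per arm = 2(1.96 + 0.84)² SD² / 0.20². An SD of 0.64 gives 161 per arm, or 404 in total after 20% loss. That SD serves only as the residual SD in step 4.

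**Step 1. Household-level screen.** SE = √(2/200) = 0.10 SD, so any observed difference below 1.96 × 0.10 = 0.196 SD is non-significant. With a true difference of 0.20, P(miss) = Φ(1.96 − 2.00) − Φ(−1.96 − 2.00) = 0.48.

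**Step 2. Cluster-level screen.** SE = √[(2/4)(ICC + (1 − ICC)/50)], referred to non-central t with 6 df (critical value 2.45).

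| ICC | SE (SD) | 0.20/SE | P(miss) |
|---|---|---|---|
| 0.02 | 0.141 | 1.42 | 78% |
| 0.05 | 0.186 | 1.08 | 85% |
| 0.10 | 0.243 | 0.82 | 89% |

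A normal-theory test with design effect 1 + 49 × ICC gives 70%, 81% and 87%.

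**Step 3. Bias when the screen misses.** Missed studies have smaller realised imbalance than 0.20 SD, because the larger ones are flagged. The mean given a miss is:

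- household test: 0.118 SD (truncated normal);
- cluster test: 0.155-0.161 SD (simulation, ICC 0.02-0.10).

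Bias = realised imbalance × effect per SD:

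- lowest: 0.118 × 0.1 = 0.012 HAZ, and 0.012/0.20 = 6%;
- highest: 0.161 × 0.4 = 0.064 HAZ, and 0.064/0.20 = 32%.

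**Step 4. The rule averaged over all studies, flagged or not.** A simulation of 4,000 runs per setting used independent households, 160 v 160 analysed, residual SD 0.64, no treatment effect and all confounders measured. The outcome test was one-sided at 5%.

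| Confounders | Imbalance (SD) | Effect (HAZ per SD) | Screened: mean bias | Screened: type I error | Full set: type I error |
|---|---|---|---|---|---|
| 1 | 0.20 | 0.20 | 0.013 | 7.1% | 5.4% |
| 3 | 0.15 | 0.15 | 0.033 | 10.9% | 5.3% |
| 5 | 0.15 | 0.10 | 0.034 | 11.5% | 4.5% |

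Mean bias with the full set was about zero (0.003 or less in size). All simulated imbalances ran in one direction; opposing ones would partly cancel.

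**The case against.** **Design features.** The listed community characteristics are handled by matching, the change-score analysis removes fixed differences in level, and age, sex and baseline outcome are always adjusted for. This stands as mitigation. It does not cover household-level factors, such as wealth or diet, that affect growth over the 12 months. Matching communities does not balance the households within them.

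**Open wording.** A reader might infer that the plan drops the confounders it names. The text does not go that far: the covariate list is introduced as inclusive, and Study measures says the extra variables are assessed to control confounding. But the only rule the Analysis section states for admitting further child covariates is the significance screen, so they can be left out.

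**Propensity trigger.** It refers to important differences rather than p-values, so it could catch what the screen misses. The Sample size section offers propensity matching as an example, and the Analysis section can be read as saying when it applies. A flat contradiction is therefore too strong, and a numerical threshold could sit in an analysis plan not shown. What remains is that one section promises such techniques during analysis and the other makes them conditional. The two need aligning.

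**Size.** A reader might multiply the whole 0.20 SD by an effect of 0.2-0.4 and get 0.04-0.08 HAZ, or 20-40% of target. That overstates the bias in missed studies, for the reason in step 3. A reader might also infer confidence intervals that are too narrow. Nothing here shows that: interval widths were not computed, and the type I error inflation in step 4 comes with a shifted estimate.

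**Conclusion.** The concern holds for the child outcomes. The article states a selection rule, so this is not detail deferred to another document, and an analysis plan that followed the rule would inherit the weakness. A 0.20 SD imbalance would be missed in about half of studies under a household-level test, and in roughly four-fifths or more under a cluster-level one. The resulting bias is about 0.01-0.06 HAZ per missed confounder, or 6-32% of the 0.20 target.

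The miss rates rest on the assumed imbalance, cluster layout and ICC. The bias also rests on an assumed effect per SD for which the article gives no source. The weakness of the rule does not depend on those values. The screen does not govern age, sex, the baseline measure or the named yield covariates.

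**What to change.** For the child-outcome models only, replace the significance rule with a prespecified set of household-level baseline covariates, used whatever their p-values:

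- child age and sex;
- the corresponding baseline measure;
- maternal education;
- household consumption and assets;
- usual diet;
- child illness;
- household decision making.

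Keep community-level covariates to a minimum, because clusters are few. A matched-pair term, for example, would cut cluster-level degrees of freedom from 6 to 3 if 4 v 4 clusters formed four pairs, and raise the critical t from 2.45 to 3.18. Do not adjust for gear type where arm determines it; the trap arm targets basket-trap fishers. Leave the named fisheries-yield covariates as they are.

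Reconcile the Sample size and Analysis sections by planning one propensity-score analysis as a sensitivity analysis, run regardless of observed imbalance, with balance reported as standardised differences.

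The cost is revised wording, a few household-level degrees of freedom and one extra model. The household survey already covers these domains at baseline, and the sample size does not change.

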**Methods:**

There will be 400 small-scale fisher households enrolled from Kilifi County, Kenya and residing in communities matched on location (rural), livelihoods, and child nutritional status. The sample will include mothers and other caregivers, children 6–60 months, and fishers in the family. Applying a cluster design, the matched communities will be divided into three groups: (1) control (*n* = 200); (2) multi-component nutrition social marketing intervention to fishers, mothers, and health workers (*n* = 100); and (3) multi-component nutrition social marketing intervention plus modified fishing traps and training (*n* = 100). Primary outcomes include child growth, fish food intakes, and fisheries yield of mature fish. Secondary outcomes are diet diversity, child diarrheal morbidity, and fisheries revenue. A process evaluation will be used to monitor and ensure fidelity of intervention delivery.

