## Methods and analysis

### Design

We aim to test the effectiveness of the multi-component *Samaki Salama* intervention as it intersects with nutrition security and fisheries sustainability in Kilifi County, Kenya. Table 1 details the specific aims and hypotheses.

**Table 1 T1:** Study aims and hypotheses.

**Study aims**	**Hypotheses**
1. Determine the effects of a multi-component social marketing campaign to promote fish nutrition, dietary diversity, and food safety on child growth	**Primary** Hypothesis 1: Children in combined intervention groups have increased height-for-age *Z* by 0.2 compared to children in the control Hypothesis 2: Children in combined intervention groups have increased weight-for-age *Z* by 0.10 compared to children in the control Hypothesis 3: Children in combined intervention groups have increased fish food intakes by 100 g compared to children in the control
	**Secondary** Hypothesis 4: Children in combined intervention groups have increased dietary diversity by 1.2 compared to children in the control Hypothesis 5: Children in combined intervention groups have reduced diarrheal morbidity by 5 percentage points compared to children in the control
	**Exploratory** Hypothesis 6: Children in the social marketing + traps intervention group have increased dietary diversity and fish intake compared to children in the social marketing only group
2. Measure the impact of modified fishing traps with escape gaps on catch dynamics and earnings	**Primary** Hypothesis 7: Fishers in the social marketing + traps intervention group have significantly increased fisheries yields of mature fish compared to fishers in the control
	**Secondary** Hypothesis 8: Fishers in the social marketing + traps intervention group will have significantly increased earnings compared to fishers in the control

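### Aim 1 has three co-equal primary hypotheses, each tested at the full one-tailed 5%, with no lead hypothesis and no division of alpha

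*Protocol article*

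**What the plan says.** Table 1 (Design) lists three hypotheses as primary under Aim 1:

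- H1: "Children in combined intervention groups have increased height-for-age" Z, by 0.2.
- H2: "Children in combined intervention groups have increased weight-for-age" Z, by 0.10.
- H3: "Children in combined intervention groups have increased fish food intakes by 100 g compared to children in the control".

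Aim 2 has one primary hypothesis, H7: "Fishers in the social marketing + traps intervention group have significantly increased fisheries yields of mature fish compared to fishers in the control". The abstract lists the outcomes without ranking them: "Primary outcomes include child growth, fish food intakes, and fisheries yield of mature fish".

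The Analysis section (Primary and secondary outcomes) says that effectiveness is tested with the two intervention groups pooled, apart from named exceptions that do not touch H1 to H3. It then gives a single error level for all outcomes. The "significance value for Type I error (and one-tailed test) will be" P < 0.05, "and corresponding 95% confidence interval".

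The Sample size section uses a mean HAZ of −1.3 and "a hypothesized 0.20 effect size", with alpha 0.05 and power 0.80. It does not mention WAZ or fish intake, and it does not call HAZ the lead hypothesis.

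**The concern.** An error level of 5% describes one test. Aim 1 has three tests of primary rank, on the same contrast and in the same children, and each may use the whole 5%. The article does not say how the three results combine into a conclusion for the aim.

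The three results could well differ. Feeding fish daily is one of the four behaviours that the campaign promotes directly (Interventions), so intake is close to the intervention. Aim 1, however, is worded as an effect on child growth, which lies further along the pathway in the Logic framework. A report could call the intervention effective on a primary outcome because of intake alone while both growth measures show nothing. The stated 5% would not be the error rate of that statement.

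**Working it through.** **Inputs from the protocol article**

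- Number of Aim 1 primary tests: k = 3 (Table 1: H1, H2, H3).
- Level per test: one-tailed 0.05 (Analysis), so the critical value is z = 1.645.
- Contrast: combined intervention versus control for all three (Table 1 and Analysis agree).

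**Input not in the document:** the correlations between the three test statistics. I assume a common value ρ and show a range.

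**The plan's own figures.** One test at z > 1.645 has a false-positive probability of 0.05, as stated. The 400 households cannot be reproduced, because neither the SD of HAZ nor an intracluster correlation is given. The multiplicity point does not depend on that number.

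**Probability of at least one false positive in Aim 1, with no true effect on any of the three**

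For independent tests: 1 − (1 − 0.05)³ = 1 − 0.857 = 0.143.

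For correlated tests: 1 − Φ₃(1.645, 1.645, 1.645; ρ), where Φ₃ is the trivariate normal distribution function.

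| ρ (assumed) | Rate | Multiple of 5% |
|---|---|---|
| 0 | 14.3% | 2.9 |
| 0.3 | 13.0% | 2.6 |
| 0.5 | 11.8% | 2.4 |
| 0.7 | 10.3% | 2.1 |
| 0.8 | 9.3% | 1.9 |

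A common ρ is a simplification, since the two growth scores should be more closely related to each other than to intake. With 0.7 between HAZ and WAZ and 0.2 between each of them and intake (also assumed), the same calculation gives 12.2%, inside the range.

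**Sensitivity to the level.** A two-sided 95% interval corresponds to a one-sided level of 0.025. If 0.025 were the level used, three independent tests would give 1 − 0.975³ = 7.3%, still 2.9 times the level per test.

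**After the fix**

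- HAZ as the single deciding test, or first in a fixed sequence: 5%.
- Holm across three: the smallest P must be below 0.05/3 = 0.0167. The chance of any false positive is at most 3 × 0.0167 = 5%; for independent tests it is 1 − (1 − 0.0167)³ = 4.9%.

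**Power cost of Holm.** Take a test with exactly 80% power at one-sided 0.05. Its expected z is 1.645 + 0.842 = 2.487. At Holm's first step the critical value is 2.128, so power there is Φ(2.487 − 2.128) = Φ(0.359), about 64%. This is the worst case for that test: if another hypothesis has already been rejected, its threshold relaxes to 0.025 and then to 0.05.

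**The case against.** The strongest reply is that this is an omission which the rules for a condensed article excuse. Hierarchy and multiplicity are usually set out in the statistical analysis plan, which is not shown. On that view P < 0.05 is a generic level, and each hypothesis can be reported separately at its own 5%. Part of this stands. The article defines no rule for trial success, so the 9% to 14% applies only if any one success is read as effectiveness. But the article is not silent on the level. It gives three hypotheses primary rank under one aim and then fixes the full one-tailed 5% for each outcome it tests. An analysis plan that divided alpha would depart from this text.

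A reader might go further in three ways that the document does not support.

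- **Counting four primaries by adding fisheries yield.** This gives up to 1 − 0.95⁴ = 18.5%. H7 belongs to a different aim, with different participants and different data. Treating it as a separate claim with its own 5% is reasonable, so the four-test figure is not the right size for this point.
- **Saying that the comparison is undefined.** For H1 to H3 it is fixed as combined intervention versus control. What is missing is a lead hypothesis. Only for H7 do Table 1 (traps group versus control) and the Analysis section (pooled groups) disagree, which is a separate matter to reconcile.
- **Saying that the plan declares success on whichever test crosses 0.05.** No section says so.

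It is also fair to object that putting fish intake behind HAZ is debatable. If HAZ is underpowered, the gate could block confirmation of a real effect on intake. For this reason the fix offers two routes.

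Finally, the calculation takes each test to hold its nominal 5%. In a non-randomised design with about four clusters per arm that is itself uncertain, so the rates should be read as approximate.

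**Conclusion.** The point holds for Aim 1. Three co-equal primary hypotheses on the same contrast are each tested at the full one-tailed 5%, with no lead and no division of alpha, while the sample size rests on one of them. If success on any one is taken as effectiveness, the Aim 1 false-positive rate is about 9% to 14%, central value 11.8%, roughly two to three times the stated 5%. This rests on assumed correlations from 0 to 0.8, no true effect on any of the three outcomes, and tests that hold their nominal level. The plan is not invalidated, but the rule should be settled before the outcome data are analysed.

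**What to change.** Amend Table 1 and the Analysis section in one of two ways:

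1. Name H1 (HAZ, combined intervention versus control) as the single deciding primary for Aim 1, since it is the only outcome the sample size was computed for. Test WAZ and fish intake after it, each only if the one before is significant and in a stated order, or make them secondary.
2. Keep H1, H2 and H3 as primary and apply Holm across them: smallest P below 0.0167, next below 0.025, last below 0.05.

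Under either route, state that H7 is the separate primary of Aim 2, that each aim's conclusion is reported separately, and that all estimates and intervals are reported whatever the tests show.

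The cost is a few sentences and no new data. Under route 1, HAZ keeps its full alpha, but WAZ and fish intake can be claimed as confirmed only if HAZ succeeds, or not as primary results at all. The sponsor should weigh that against the power it really expects for HAZ. Under route 2, intake does not depend on HAZ, but all three face a stricter first threshold, and a test planned at 80% power has about 64% at that first step.

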**Primary outcomes**			
Child growth	Anthropometric measures of height and weight	Length-for-age *Z* score (LAZ) Weight-for-age *Z* score (WAZ) Weight-for-length *Z* score (WLZ)	Baseline, 12 mo.
Fish food intakes	24-h intake survey	Fish food intakes in g	Baseline, 12 mo.
Fisheries yield of mature fish	Fish catch survey at landing sites	Monthly catch per unit effort and fish size distribution	5–10 times per month at randomly stratified days over the course of 12 months

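### The one-tailed P < 0.05 rule does not correspond to the 95% confidence interval paired with it, on the ordinary two-sided reading of that interval

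*Protocol article*

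**What the plan says.** The Analysis section, under Primary and secondary outcomes, gives one rule without limiting it to particular outcomes: "and one-tailed test) will be *P* < 0.05 and corresponding 95% confidence interval". It gives no reason for testing in one direction and mentions no one-sided confidence bound.

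The Sample size section gives its error rates as "assuming 20% losses-to-follow-up (α = 0.05 and 1-β = 0.80", without saying whether that alpha is one- or two-sided. The other inputs there are a mean HAZ of −1.3, "a hypothesized 0.20 effect size", and the conclusion "we estimate requiring a total sample size of 400 households". No standard deviation or intracluster correlation is stated.

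All the hypotheses in Table 1 point towards benefit: more growth, more fish eaten, more varied diets, less diarrhoea, more mature fish caught and higher earnings.

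**The concern.** A significance rule and the interval reported beside it should lead to the same decision. Here the text says that they correspond, but a one-tailed 5% test is more lenient in the hoped-for direction than a two-sided 95% interval. For a band of results, the P value would support a claim of benefit and the interval would not. The protocol does not say which prevails, and the sentence covers every primary and secondary outcome.

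Two things follow. First, the false-positive risk in the favourable direction is higher than a reader of a 95% interval would assume. That matters more in a non-randomised comparison with about four clusters per arm, where a positive result already needs cautious reading. Second, a test aimed only at improvement has no way to declare a deterioration. Fisher earnings show why this is relevant: fathers are asked to hold back some of the catch for the child each day, and revenue is recorded from fish sold, so lower earnings are conceivable on the protocol's own description.

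**Working it through.** **Inputs.** From the Analysis section: one-tailed test, threshold 0.05, 95% interval. From Sample size and Table 1: HAZ effect 0.20, alpha 0.05, power 0.80, 20% loss, 400 households. From Participant eligibility, recruitment, and retention: 200 control and 100 + 100 intervention, so 200 against 200 when the intervention groups are combined.

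**1. Does the stated pairing reproduce?**
- One-tailed 0.05: critical z = 1.645. The two-sided interval with that multiplier has coverage 1 − 2 × 0.05 = 90%.
- Two-sided 95% interval: multiplier z = 1.960. The matching one-tailed level is 0.05 / 2 = 0.025.

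The pairing as written does not reproduce.

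**2. Where the two halves conflict.** For z between 1.645 and 1.960 (one-sided P from 0.025 to 0.05, two-sided P from 0.05 to 0.10), the rule declares benefit and the 95% interval includes no effect. An illustration, with an *assumed* standard error of 0.11 because the article gives no figure from which to derive one:
- estimate 0.20 (the hypothesised HAZ effect); z = 0.20 / 0.11 = 1.82; one-sided P = 0.034
- 95% interval: 0.20 ± 1.960 × 0.11 = −0.016 to 0.416

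The hypothesised effect itself would then be significant by the test and not by the interval.

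**3. False claims of benefit with no true effect.** One-tailed 0.05 gives 5.0% per test. Two-sided 0.05 gives 2.5% in the favourable direction. The ratio is 2.0.

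**4. Effect on power.** The required sample size is proportional to (z for alpha + z for power)², with z = 0.842 for 80% power.
- One-sided sum: 1.645 + 0.842 = 2.486. Two-sided sum: 1.960 + 0.842 = 2.802 (from unrounded values).
- If 400 was sized one-sided: two-sided power = Φ(2.486 − 1.960) = Φ(0.526) ≈ 70%. Keeping 80% would need 400 × (2.802 / 2.486)² ≈ 508 households, about 27% more.
- If 400 was sized two-sided: the stated 80% is unchanged by the fix, and the one-tailed rule now in the text would give Φ(2.802 − 1.645) = Φ(1.157) ≈ 88%.

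**5. Can the sample size show which was used?** After 20% loss, 200 × 0.8 = 160 per side. With no design effect, the SD that gives exactly 80% power is 0.20 / [√(2/160) × sum]: 0.72 one-sided or 0.64 two-sided. Since neither an SD nor an intracluster correlation is stated, 400 fits either sidedness and does not settle the question.

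**The case against.** The best defence is that the interval need not be two-sided. A one-sided 95% bound corresponds exactly to a one-tailed test at 0.05, and the sentence does not use the word two-sided. That reading is possible, but nothing in the article supports it: no bound is mentioned, and an unqualified 95% confidence interval is ordinarily taken as two-sided. At the least, the sentence needs to say which is meant.

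One-tailed testing is also a recognised choice when it is specified in advance, and the Table 1 hypotheses are directional. This stands as an explanation for the test. It does not make the test agree with an ordinary 95% interval. It is also true that a reported two-sided interval could reveal an adverse effect even though the test could not declare it.

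Some stronger conclusions might be inferred that the documents do not support:
- *The rule doubles the chance of claiming benefit.* This is exact only when there is no effect. Under a real effect the gain is smaller: 70% to 80%, or 80% to 88%, in the two cases worked above.
- *Yield could fall and go undeclared for the same reasons as earnings.* The outcome is yield of mature fish. The Logic framework says that the escape gaps release immature fish and keep mature ones, and the catch is weighed on return from fishing, so fish taken home afterwards does not lower the measured yield.
- *The primary outcomes are tested with no control of multiple testing.* Such a procedure is commonly left to an analysis plan, which is not shown here, so its absence from a condensed article is no finding.
- *The rule is also applied to weight-for-length.* Table 5 lists "Weight-for-length *Z* score (WLZ" among the primary indicators, but the Analysis section does not name it among the outcomes to be modelled.
- *The study loses power under two-sided testing.* The stated power falls only if the 400 households were sized one-sided, and the article does not say.

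**Conclusion.** The point holds as a mismatch within one sentence. Read in the ordinary way, the test and the interval do not correspond, and any result with one-sided P between 0.025 and 0.05 would be declared a benefit against a 95% interval that includes no effect. With no true effect, the risk of a false claim of benefit is 5% per test instead of the 2.5% that the interval implies. The rule cannot declare a worsening, for which earnings is the credible example.

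The conclusion assumes that the interval is the usual two-sided one. The 5% and 2.5% figures are nominal, per test, and take the standard errors as valid. The power figures are conditional on the stated 80% being correct for whichever sidedness was used, which the article does not allow a reader to check.

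**What to change.** In the Analysis section, replace the rule with two-sided tests at 0.05 (equivalently one-sided 0.025) and two-sided 95% confidence intervals for the primary and secondary outcomes. Under Sample size, state the sidedness of the 0.05 alpha, and make it the same.

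Suggested wording: *All tests of primary and secondary outcomes will be two-sided at a significance level of 0.05, and estimates will be reported with two-sided 95% confidence intervals.*

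Keeping the one-tailed 0.05 test and reporting a two-sided 90% interval or a one-sided 95% bound would also remove the inconsistency. It would leave the 5% false-benefit risk and the inability to declare a worsening in place, so it is the weaker option and would need a stated justification.

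The cost is wording, best settled before outcomes are analysed. If the sample size was calculated one-sided, the stated power should be restated as about 70%, or about 508 households would be needed to keep 80%. If it was calculated two-sided, neither the sample size nor the stated power changes.
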